The present intervention protocol addresses childhood obesity in an integrative and unconventional manner, generating multifactorial knowledge about family behavior, individual factors, and the school environment. The aim of this protocol is to measure the effect of an intervention designed for low-income Mexican schoolchildren, focused on promoting healthy lifestyles for the prevention of obesity and cardiometabolic diseases. Specific aim 1 is to analyze whether baseline anthropometric and behavioral variables are associated with psychosocial well-being, family interaction or functionality, and perceptions of childhood obesity in the home environment. Specific aim 2 is to evaluate the effectiveness of the intervention in terms of retention, motivation to change, fidelity, and acceptability of the program by schoolchildren. Specific aim 3 focuses on evaluating changes in health behaviors at the end of the intervention and after 6 months in knowledge, diet quality, exercise time, and sleep time and quality.

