#### Effectiveness

Results obtained in the experimental arm will be compared with those of the control arm to analyze the significant differences in behavioral and health outcomes between them. This comparison will provide a more robust perspective on the real impact of the intervention on the habits and health of the participants [69].

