### Statistical Analysis

The normal distribution of the data will be verified using skewness, kurtosis, and Kolmogorov-Smirnov tests. Quantitative data with nonnormal distribution will be mathematically transformed for parametric analysis, or alternatively, nonparametric analysis will be used. Means and SDs will be calculated for continuous variables and percentages for categorical variables. To test age, sex, socioeconomic status, and location baseline differences, we will use chi-square tests for qualitative demographic variables (eg, socioeconomic level, family medical history, sport practice, etc) and analysis of covariance for quantitative variables (eg, anthropometrics, dietary intakes, HEI, TMexD, sleep time, BIP, family interaction, and psychosocial well-being). To evaluate specific aim 1, potential baseline associations of dependent variables (eg, anthropometrics and blood pressure) with independent behavioral variables (eg, dietary intakes, exercise and sleep time, family interaction, psychosocial well-being, and perception of childhood obesity) will be tested using multiple linear regression, starting with univariate regression (*P*<.2 and biological plausibility). Models will be built by a combination of univariate analysis and forward stepwise model selection using *P*≤.05 and biological plausibility. Preliminary models will be assessed for possible interactions (*P*≤.1) between sex and other variables included in the model, for collinearity (variance inflation factor<10), and for linear regression assumptions (linearity, normality, and homoscedasticity) using residual plots. Specific aim 2 will use mixed methods (qualitative and quantitative) to analyze results in terms of retention, fidelity, and acceptability of the intervention by children and school administrators. Specific aim 3 will compare the changes between the experimental arms (intervention vs control) from baseline to postintervention and to the 6-month follow-up in anthropometrics, blood pressure, HEI, dietary intakes, PA, sleep time, and knowledge. Primary analyses will follow the intention-to-treat principle. Given the hierarchical structure of the data (students nested within classrooms and classrooms within schools) and the repeated measurements over time (baseline, postintervention, and 6-month follow-up), intervention effects will be evaluated using multilevel mixed-effects regression models. Due to the cluster-based allocation, the intraclass correlation will be considered, potential attrition will be monitored, and all analyses will account for clustering to provide valid inferences. Models will include fixed effects for study arm, time, and the arm×time interaction, and random effects for classroom and school to account for intracluster correlation. Baseline values of the outcomes and covariates will be included as appropriate. Effect estimates with 95% CIs will be reported. We will examine model assumptions and fit indices. SPSS (IBM SPSS Statistics version 21.0) and STATA (StataCorp version 14.0) software will be used, with a *P* value <.05 for all statistical analyses.

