## Discussion

Lifestyle interventions in early life are critical to reducing future disease risk and health care costs. During recent years, most of the research has been toward adult behavior [23], but recently, successful programs have been adapted to children and adolescents [21,33], representing an opportunity to extend their benefits to youth. For a greater probability of success, participant and setting characteristics should be accounted for. Places where children spend most of their time are school and home; schools represent a structured environment for the implementation of planned activities, fostering knowledge acquisition and sustainable behavioral changes. Within schools, a broader population is reached, and participants support each other, sharing experiences [25,26,74].

Two main biological models have been proposed to explain obesity: the carbohydrate-insulin model [64] and the energy balance model [75], the latter reinforced by current evidence on the high energy contribution of UPFs. Our intervention is primarily based on the carbohydrate-insulin framework, which posits that diets high in rapidly absorbed carbohydrates—often from UPFs, also high in energy, saturated fat, and sodium—promote hyperinsulinemia and adiposity. Accordingly, the intervention focused on improving carbohydrate quality and overall dietary patterns by reducing UPF consumption, along with structured PA to improve insulin sensitivity and body composition, and therefore reduce obesity. Secondary cardiometabolic outcomes were examined within this same framework, given the influence of diet and PA on metabolic and vascular health. Taken together, it is hypothesized that these behavioral changes improve insulin sensitivity, inflammation, and vascular function, thereby reducing cardiometabolic risk.

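### No primary outcome is named, the outcome lists conflict, and every comparison at two follow-ups is tested at P<.05, so the chance of a false effectiveness signal is well above 5%

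*Protocol article*

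**What the plan says.** - **How effectiveness is judged.** The Effectiveness section compares the two arms "to analyze the significant differences in behavioral and health outcomes between them". No outcome is singled out.
- **Threshold.** Statistical Analysis closes "with a *P* value <.05 for all statistical analyses".
- **Aim 3 in Statistical Analysis.** Changes from baseline to each of the two follow-ups are compared "in anthropometrics, blood pressure, HEI, dietary intakes, PA, sleep time, and knowledge. Primary analyses will follow the intention-to-treat principle". The word primary describes the analysis set here and not an outcome.
- **Aim 3 in the Introduction.** The same aim covers changes "at the end of the intervention and after 6 months in knowledge, diet quality, exercise time, and sleep time and quality". Anthropometrics and blood pressure are not in it.
- **Study Design, phase 3.** A third list has knowledge, anthropometrics, blood pressure, diet quality, exercise and sleep quality, but not sleep time.
- **Discussion.** "Secondary cardiometabolic outcomes were examined within this same framework". The article names no primary outcome to which these are secondary.
- **Timing.** Ethical Considerations dates the registration July 10, 2023. Results dates recruitment from October 2023. Table 3 ticks all measurements at all four schools, and data analysis at two of them.

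**The concern.** The objective is prevention of obesity and cardiometabolic disease. A reader of the Introduction would take Aim 3 to be about behavior only, because anthropometrics enter those aims just once, as baseline variables in Aim 1. A reader of Statistical Analysis would take Aim 3 to include anthropometrics and blood pressure. Nothing in the article says which of these results decides whether the program worked.

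With many outcomes, two follow-ups, one unadjusted threshold and no ranking, an isolated P<.05 can be presented as evidence of effectiveness, and the article gives a reader no basis for discounting it. The choice also affects who is analyzed: the 24-hour recalls and the physical activity recall cover grades 4 to 6 only, whereas anthropometry is not restricted by grade.

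**Working it through.** The article states no familywise error, power or target sample size, so there is no figure of its own to reproduce. The only stated error rate is .05 per test. Two-sided testing is assumed, because sidedness is not given.

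**1. Number of tests**

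- Introduction list: knowledge, diet quality, exercise time, sleep time, sleep quality = 5. Over 2 follow-ups: 5 × 2 = 10.
- Statistical Analysis list, one test per named domain: 7 × 2 = 14.
- Statistical Analysis list, by the variables that the measurement sections define:
  - 6 anthropometric: BMI, BMI percentile, waist circumference, waist-to-height ratio, body fat, fat mass index
  - 2 blood pressure: systolic and diastolic
  - 1 HEI
  - 5 dietary: total sugars, added sugars, sodium, saturated fat, ultra-processed share
  - 2 physical activity: moderate-to-vigorous activity and total METs
  - 1 sleep time
  - 1 knowledge
  - Total 6 + 2 + 1 + 5 + 2 + 1 + 1 = 18, and 18 × 2 = 36.

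The 18 is an assumed count. The ultra-processed share comes from the NOVA section and is not named in Statistical Analysis. On the other side, weight and vigorous activity are left out, and the dietary list is open-ended.

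**2. Chance of at least one P<.05 when nothing works**

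For independent tests this is 1 − 0.95^m:

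- m = 10: 1 − 0.95^10 = 0.401
- m = 14: 1 − 0.95^14 = 0.512
- m = 36: 1 − 0.95^36 = 0.842, with 36 × 0.05 = 1.8 false positives expected at any correlation

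The article gives no correlations between outcomes. For normal test statistics with one common correlation r (an assumption):

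| Tests | r = 0 | r = 0.3 | r = 0.5 | r = 0.6 |
|---|---|---|---|---|
| 10 | 40% | 35% | 29% | 25% |
| 14 | 51% | 44% | 35% | 30% |
| 36 | 84% | 72% | 55% | 45% |

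A second structure was simulated with 200,000 draws. It assumed correlation 0.3–0.8 within a domain, 0–0.3 between domains and 0–0.7 between the two follow-ups. It gave 42–51% for 14 tests and 58–82% for 36.

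**3. If each outcome has one joint arm×time test**

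- 7 domains: 1 − 0.95^7 = 0.302.
- 18 variables: 1 − 0.95^18 = 0.603 if independent, and 42–57% in simulation with correlated outcomes.

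**4. After the fix**

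One primary outcome at one time point gives 5%. One outcome at two time points, each at .025, gives 1 − 0.975^2 = 0.049.

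**5. Share of the sample marked as analyzed in Table 3**

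(173 + 117) / 451 = 290 / 451 = 64%.

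**The case against.** **Unseen documents.** The trial was registered before recruitment, and a full analysis plan may exist. Either could name a primary outcome, and a multiplicity procedure is commonly left to the analysis plan. This stands as far as it goes: the absence of a procedure is not in itself a fault of a condensed article. It does not answer what the article does state, namely one threshold for all analyses, an effectiveness comparison over all outcomes, and outcome lists that disagree. An unseen plan does not reconcile those sections.

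**No literal win-on-any rule.** A reader might infer that one significant result is enough to declare effectiveness. The Effectiveness section does not say so. Statistical Analysis promises effect estimates with 95% CIs, and Aim 2 ties effectiveness to retention, motivation, fidelity and acceptability. The article leaves that use open but does not prescribe it.

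**More likely than not.** A reader might conclude that a false positive somewhere is more probable than its absence. That depends on the count and the correlation. It holds for 36 tests at r up to about 0.5 but not at 0.6 (45%). It is marginal for 14 tests (51% at best) and fails for 10 (40% at best). BMI with BMI percentile, or the same outcome at two follow-ups, may well be strongly correlated.

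**Table 3.** A reader might infer that 64% of the children have already been compared by arm. The table does not show that. The tick may cover baseline work only, and data interpretation is blank for all four schools.

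**Implied order.** The Discussion puts obesity ahead of the cardiometabolic outcomes, which hints at a ranking. It names neither a variable nor a time point.

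**Conclusion.** The concern holds on the article's own text. No outcome has primary status although the article uses both primary and secondary as labels. The outcome lists in the Introduction, Study Design and Statistical Analysis conflict. Change in adiposity or blood pressure is in none of the Introduction's specific aims. All comparisons at two follow-ups carry the same .05.

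With no true effect on any outcome, the chance of at least one P<.05 is about 25–40%, 30–51% or 45–84% for 10, 14 or 36 tests. That is at least five times the nominal 5% in each case. The ranges rest on the assumed counts, equal correlations of 0 to 0.6, and a separate test at each follow-up; joint testing would lower them. That the figure changes with the list a reader uses is part of the problem.

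The tick for 290 of 451 children does not show that the outcome choice has been influenced by results. It does mean that the choice needs to be traceable to a record older than the data.

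**What to change.** 1. State one primary outcome at one time point, taken from the July 2023 registration, and claim effectiveness only on that outcome at two-sided .05.
2. If the registration lists several primary outcomes or none, say so, and disclose that the choice was made after the data were captured. Rewording cannot restore prespecification in that case.
3. Align the outcome lists in the Introduction, Study Design and Statistical Analysis, including whether anthropometrics, blood pressure, sleep time and sleep quality belong to Aim 3.
4. Label all other outcomes secondary or exploratory, or put them under Holm or false-discovery-rate control, and limit the blanket .05 sentence accordingly.
5. State what the data analysis already ticked in Table 3 covered, in particular whether arms were compared.

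This needs changes to the text and no new data. The cost is that an isolated P<.05 on another outcome can no longer be called effectiveness.

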The age of participants may also limit their responses, since younger schoolchildren find it difficult to express themselves and remember data (ie, quantity of food and time of PA). This could be improved through greater interaction between staff and participants to build trust and facilitate recall of daily activities, enhancing the accuracy of responses. Regarding the self-reported estimates of PA and dietary intake, they depend on short- and long-term memory, showing greater variability compared to other objective measures [85,86]. However, the 3-day physical activity recall and the 24h-R are validated instruments widely used in the child population [87,88]. The use of few repetitions of the 24h-R does not ensure the measurement of between- and within-person variability; however, administering more repetitions could increase the challenges inherent in data collection in children and adolescents, who may have difficulty sharing information about their behaviors and may experience mental burden and stress [89]. Another limitation is that other important social actors in the student’s life, such as parents, will not be involved; however, the involvement of teachers, and especially classmates, is possible. The curriculum implementation depends on the time available in the school curriculum itself; however, if the intervention begins alongside the school year, it optimizes time and makes it easier to complete it. Another opportunity for future studies is to include other crucial variables such as quality of life and self-esteem, which are important at this stage. Concerning multilevel models, these require larger sample sizes, involve more complex assumptions, and may be sensitive to model misspecification. However, these are well suited for group-randomized trials, as they account for data grouping, provide valid standard errors, accommodate missing or unbalanced data, and allow the simultaneous examination of individual- and group-level effects, thereby improving statistical efficiency and inference.

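### The Aim 3 model, as listed, has three visits per child but no child-level term, so the arm-by-time standard error is miscalibrated, in a direction that depends on classroom drift

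*Protocol article*

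**What the plan says.** The Statistical Analysis section gives two reasons for a multilevel model: the hierarchy, "students nested within classrooms and classrooms within schools", and "the repeated measurements over time (baseline, postintervention, and 6-month follow-up"). The target is a difference in change: "Specific aim 3 will compare the changes between the experimental arms (intervention vs control) from baseline to postintervention and to the 6-month follow-up". The model is then listed: "Models will include fixed effects for study arm, time, and the arm×time interaction, and random effects for classroom and school". The purpose given for the random part is intracluster correlation: "random effects for classroom and school to account for intracluster correlation". On baseline the section says only: "Baseline values of the outcomes and covariates will be included as appropriate".

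No section names a participant random effect, a within-child residual covariance or a cluster-robust standard error. The promise that analyses will account for clustering is tied to the allocation of classrooms, not to visits within a child.

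Two statements in the Discussion bear on this. The strengths paragraph credits the study with repeated-measures ANOVA, a different method from the one in Statistical Analysis. The limitations text says that multilevel models "provide valid standard errors, accommodate missing or unbalanced data".

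**The concern.** The child is named as a level of the data and then left out of the listed random effects. Given classroom and school, the model as listed treats a child's three values as independent.

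Aim 3 is about change. A child who is heavy at baseline is usually heavy later, and that stable part drops out of the child's own change. A model without a child term cannot see this, so it builds the arm×time standard error from between-child as well as within-child variation. Confidence intervals and P values for the main effect estimates then do not have their stated properties. The effect should be largest for outcomes that track strongly within a child, such as anthropometrics, and smaller for noisy recall measures. The Discussion already concedes a low sample size, so lost precision matters.

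The listed model also has no term for classrooms changing differently over time. That omission pushes the standard error the other way, so the two must be considered together.

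**Working it through.** The article states no power, standard error, ICC or within-child correlation, so there is no figure of its own to reproduce.

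**Inputs from the article.** 24 classrooms, 12 per arm (Selection of Schools). 451 children (Results; the school counts 173 + 117 + 86 + 75 = 451 agree). Mean classroom size m = 451/24 = 18.8. Significance level 0.05, taken as two-sided.

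**Assumptions.** Total variance 1, stable classroom variance 0.05, complete data. Let d be the classroom-by-time variance. The remaining 0.95 − d is split into a child part, c = rho(0.95 − d), and a within-child part, e = (1 − rho)(0.95 − d). Rho runs from 0.5 to 0.9.

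**Formulas for the arm difference in change between two visits.**
- True variance: (2/12)·2·(e/m + d)
- Variance under classroom and school effects only: (2/12)·2·(c + e + d)/m
- Variance with a child intercept added but no classroom-by-time term: (2/12)·2·(e + d)/m

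**1. No classroom drift (d = 0).** The as-written standard error is sqrt((1/3)·0.95/18.8) = 0.130 at every rho. The ratio to the true value is sqrt((c + e)/e) = 1/sqrt(1 − rho). Power is 1 − Φ(1.96·ratio − 2.80) for an effect that has 80% power under the right model.

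| rho | true SE | as-written SE | ratio | actual type I error | power instead of 80% |
|---|---|---|---|---|---|
| 0.5 | 0.092 | 0.130 | 1.41 | 0.6% | 51% |
| 0.7 | 0.071 | 0.130 | 1.83 | 0.03% | 22% |
| 0.9 | 0.041 | 0.130 | 3.16 | about 0 | under 0.1% |

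A simulation (24 classrooms of 19 children, three visits, 1,500 runs per setting) agrees: at rho 0.8 the empirical SE is 0.058 and the as-written SE 0.127.

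**2. Where the direction reverses.** The as-written variance equals the true one when c + e + d = e + m·d, that is d = c/(m − 1). Substituting c gives d = 0.95·rho/(m − 1 + rho).
- rho 0.5: 0.475/18.29 = 2.6%
- rho 0.9: 0.855/18.69 = 4.6%

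Above these values the standard error is too small. At d = 5% and rho 0.5 the true SE is 0.157 against 0.130, a ratio of 0.83 and a type I error of about 11%.

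**3. A child intercept added alone, with drift of d = 1%.** The ratio is sqrt((e + d)/(e + m·d)).

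| rho | as-written ratio | child-intercept-only ratio | type I error, child intercept only |
|---|---|---|---|
| 0.5 | 1.20 | 0.85 | 9% |
| 0.7 | 1.42 | 0.79 | 12% |
| 0.9 | 1.84 | 0.61 | 23% |

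Simulation at rho 0.8 gives type I errors of 16% at d = 1% and 25% at d = 2%. A t-test on classroom mean changes, which allows for drift, stays at about 4% in both.

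**4. Baseline as a covariate, two follow-up rows.** A simulation of this reading (24 × 19 children, classroom intercept, no child term, no drift, 400 null trials per rho) gave these ratios of model SE to empirical SE at rho 0.5, 0.7 and 0.9:
- arm effect at the first follow-up: 1.05, 1.07, 1.15
- arm effect averaged over both follow-ups: 1.02, 1.03, 1.01
- 6-month versus postintervention contrast: 1.21, 1.22, 1.45

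The last line fits the closed form. After baseline adjustment the model uses 2(1 − rho²) where the truth is 2(1 − rho), so the ratio is sqrt(1 + rho) = 1.22, 1.30 and 1.38. The averaged effect is nearly correct because the classroom intercept is estimated from classroom means, which already carry the child variation.

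**The case against.** The best defence is that the random-effects clause serves a stated purpose, intracluster correlation, and does not say that nothing else will be fitted. A within-child residual covariance is not a random effect, and a condensed article could leave it to an analysis plan. The sentence before the clause cites repeated measurements, and repeated-measures ANOVA is a within-child method. So a reader who infers that the article declares a child's visits independent goes beyond the text; it never says so. What remains is that the article does list its model terms, names the child as a level, and supplies no child term anywhere. Repeated-measures ANOVA is a competing method and does not complete the model. This is a stated specification that miscalibrates the analysis if followed.

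The second defence is the baseline sentence. It permits a follow-up-only model in which the harm to the arm effects is small (step 4). That stands, and it limits the large ratios to the three-visit model.

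The third is that the standard error is not always too large. That also stands: step 2 shows the reversal.

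**Conclusion.** The point holds in conditional form. With all three visits as outcome rows and the listed random effects only, the arm×time standard error is miscalibrated. It is too large by up to 1.41, 1.83 or 3.16 times at rho 0.5, 0.7 or 0.9 without classroom drift, and too small once drift passes roughly 2.6% to 4.6% of total variance. With baseline as a covariate, mainly the contrast between the two follow-ups suffers. The sizes rest on an assumed rho, an assumed classroom variance and complete data.

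A reader might infer that the trial's intervals are certainly too wide and its power certainly lost. The article does not support that: it gives no correlation or drift, and it leaves the role of baseline open. Nor does it follow that a child intercept by itself cures the problem; step 3 shows that it can turn a conservative test into one with too many false positives. The Discussion's claim of valid standard errors is not secured by the model as listed.

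**What to change.** Rewrite the random-effects sentence so that it names:
- a participant random intercept nested in classroom, or an unstructured within-child residual covariance over the visits;
- a classroom-by-time random effect, in addition to the classroom and school terms;
- small-sample inference suited to 24 classrooms, for example Kenward-Roger or Satterthwaite degrees of freedom where the software offers them.

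The participant term should not go in without the classroom-by-time term. The repeated-measures ANOVA statement in the Discussion should be removed or reconciled with Statistical Analysis.

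The cost is a few lines of model wording and code, and somewhat wider intervals than a child intercept alone would give. No new data are needed. Table 3 of the article marks data analysis as done for two of the four schools and interpretation for none, so the change can still precede interpretation. It should be dated and reported as made after data collection.
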